**Quantitative Objective 4. *To assess the cost-effectiveness of each ENS.***

The final objective uses data collected as part of the systems assessment. We will be capturing information on the total investment each site must make in its ENS, both in terms of financial commitments and in terms of personnel hours. This information will allow us to describe the total amount of money and effort expended in relationship to the degree of changes in services delivered, patient satisfaction, and HIV-related health outcomes. To compare these values across sites, one can standardize and combine cost variables (money + effort), then standardize outcome variables (e.g., health outcomes) and compute a ratio of <costs/outcome> for each of the six ENS. Because the ratios are standardized, one is able to compare the relative success of the six ENS at promoting desired outcome changes at lower costs. Cost effective systems are those that achieve relatively greater (desired) changes for relatively less money or personnel hours expended.

1. **Sample Size**

The table below helps display how many participants are being collected at each site per wave.

| **Method** | **Population** | **Sample size/**  **Demonstration Site/Wave of Assessment** | **Number of Assessments** |
| --- | --- | --- | --- |
| **Key Informant interviews (Component 1)** | Project Staff and Key Collaborators | Up to 7 | Two assessments: Before ENS rollout and in Year 3 of Initiative |
|  | Users of the ENS | Up to 10 | Two assessments: Before ENS rollout and in Year 3 Initiative |
|  | Patients | Up to 10 | One assessment: In Year 3 of Initiative |
| **Surveys**  **(Component 2-4)** | Systems survey  (Component 2) | 1 survey completed for each site per wave (completed via combined interview with project director and network administrator) | Six assessments: Before ENS rollout; every 6 months after rollout (total of 4 assessments); at the end of Initiative |
|  | Users Survey (Component 3) | Entire population (about 20 per site) | Five assessments: Before ENS rollout and every 6 months after rollout (total of 4 assessments post rollout) |
|  | Patients Survey  (Component 4) | 100 | Five assessments: Before ENS rollout and every 6 months after rollout (total of 4 assessments post rollout) |
| **ENS data abstraction (Component 5)** | Patients | 100 | Five assessments: Before ENS rollout and every 6 months after rollout (total of 4 assessments post rollout) |

For **Key Informant Interviews**, we may interview up to 17 project staff and ENS users per site before ENS rollout and again in Year 3 of the HRSA-sponsored Initiative. It is likely, but not guaranteed, that many of these individuals will be the same across the two waves. In the event that all interviews are with different individuals, then we will speak with a total of 204 individuals (17 per site per wave; 6 sites; 2 waves). We also will interview 10 patients per site in Year 2 of the Initiative (total: 60). **Thus, the total maximum number of unique individuals that may be interviewed is up to 264.** We based the projected number of interviews on our prior work as an evaluation center of HIV prevention services in clinical settings. The 264 key information interview participants will be enrolled by UCSF.

For the **systems survey**, we will complete one survey per site per wave (total of six waves of assessments). To complete these surveys, we must interview project personnel with knowledge of both the ENS and of the project expenses. As such, we will likely talk to both the local project director and the local network administrator at each site for each wave of data collection. (Note: the people interviewed at each site at each wave will complete the survey together. In other words, we will interview two people per site per wave in order to obtain one completed survey per site per wave.) The participants will likely be the same across waves. In the event that the interviewed individuals are different at each wave, then will speak with **up to 72 unique individuals** (2 people site per wave; six sites; six waves). The systems survey is meant to capture accurate the current configuration of the system. We are opting to include in the interviews those people most likely to have relevant knowledge about the system. The 72 people interviewed for the systems survey will be enrolled as participants by UCSF.

For the **user survey**, we will seek to interview the entire population of users at the sites. The exact number of users differs by site, but is an average of about 20. The same users will likely be assessed across waves. However, if all users are unique at each wave, then the total number of people interviewed will be **up to 600 unique individuals** (20 people per site per wave; six sites; five waves). Because the total population of users at each site is relatively small, we are seeking to survey them all in order to maximize statistical power for analyses. Users will enrolled as participants at UCSF.

For the **patient survey**, we will seek to interview 100 individuals per wave. If all individuals are unique at each wave, then we may survey **up to 3000 unique individuals** (100 people per site per wave; 6 sites; 5 waves). A sample of 100 per site (N=600 per observation period) will give us 80% power to detect 10% change in proportional outcomes (e.g. 50% to 60%) in the underlying popluation using a two-sided test with 0.05 alpha. This estimate assumes an intra-class correlation (ICC) of 0.005. ***Participants in this survey (except pilot test subjects) will be enrolled at the local sites via procedures approved by the local IRB. UCSF will only receive de-identified data for secondary analyses.***

For the **ENS data extraction**, we will seek to obtain de-identified data on 100 individuals per wave. (Note: these individuals do NOT have to be the same people who participate in the patient survey.) If all individuals are unique at each wave, then we may obtain data on **up to 3000 people** (100 people per site per wave; 6 sites; 5 waves). A sample of 100 per site (N=600 per observation period) will give us 80% power to detect 10% change in proportional outcomes (e.g. 50% to 60%) in the underlying popluation using a two-sided test with 0.05 alpha. This estimate assumes an intra-class correlation (ICC) of 0.005.. ***Data extraction is conducted at the local sites via procedures approved by the local IRB. UCSF will only receive de-identified data for secondary analyses.***

**If every participant were unique (across all components), then up to 6936 individuals could contribute data to the study.**

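### Objective 4 compares the six network systems by dividing standardized cost by standardized outcome; with ordinary z-scores this ratio cannot tell a cheap, effective system from a dear, ineffective one

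*Protocol*

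**What the plan says.** In the Protocol, Statistical Analysis, Quantitative Objective 4, each site's investment is to be captured "both in terms of financial commitments and in terms of personnel hours". The section first promises a description of the "total amount of money and effort expended in relationship to the degree of changes in services delivered", in patient satisfaction and in HIV-related health outcomes.

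For comparison between sites it then offers one index: "standardize and combine cost variables (money + effort), then standardize outcome variables (e.g., health outcomes) and compute a ratio of <costs/outcome>", calculated "for each of the six ENS". The justification is: "Because the ratios are standardized, one is able to compare the relative success of the six ENS at promoting desired outcome changes at lower costs". The section closes with the criterion that the index has to serve: "Cost effective systems are those that achieve relatively greater (desired) changes for relatively less money or personnel hours expended".

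The section does not say which standardization is meant, which direction of the ratio is favourable, or what happens when the denominator is negative or close to zero.

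**The concern.** The section contains a formula, a claim that the formula gives comparable values, and a definition of what a good value must mean. Under the ordinary meaning of standardization these three do not fit together. A z-score is negative for every system below the mean, so the cost term and the outcome term each change sign within the six systems. Dividing one by the other keeps only whether the two signs agree. It discards which of the two is negative, and that is what separates a good buy from a bad one.

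What is at stake is the answer to the cost-effectiveness objective. Cost-effective improvement is also part of the third evaluation question under Hypothesis, and Aim 3 is to disseminate findings so that they influence policy. An analyst who followed the formula with z-scores could report the best and the worst system as equivalent, or place a dominated system (dearer and less effective) ahead of the one that dominates it.

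**Working it through.** The protocol gives no cost or outcome values and no figure to reproduce, so the check is algebra plus an example with assumed values.

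**Algebra.** Let c be a system's combined standardized cost and o its standardized outcome change, oriented so that larger is better, both centred at zero across the six systems. The index is c/o. For positive a and b:

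- cheap and effective: (-a)/(+b) = -a/b
- dear and ineffective: (+a)/(-b) = -a/b
- cheap and ineffective: (-a)/(-b) = +a/b
- dear and effective: (+a)/(+b) = +a/b

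The first two are identical, and so are the last two. Reading low or high values as favourable makes no difference, because equal numbers stay equal.

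**Example (assumed values).** Money 100, 200, ..., 600 (thousand dollars); personnel hours 1000, 2000, ..., 6000; outcome change 15, 12, 10, 8, 6, 3 points. System 1 is cheapest and best; system 6 is dearest and worst.

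- Money: mean 350, SD = √(175000/5) = 187.1. System 1: z = (100 - 350)/187.1 = -1.336. Hours give the same z, so c = -2.673.
- Outcome: mean 9, SD = √(92/5) = 4.290. System 1: o = (15 - 9)/4.290 = 1.399.
- System 1 ratio: -2.673/1.399 = -1.911. System 6 ratio: 2.673/(-1.399) = -1.911.

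| System | c | o | c/o | o minus re-standardized c | uncentred (x/SD) ratio |
|---|---|---|---|---|---|
| 1 | -2.673 | 1.399 | -1.911 | 2.74 | 0.31 |
| 2 | -1.604 | 0.699 | -2.293 | 1.50 | 0.76 |
| 3 | -0.535 | 0.233 | -2.293 | 0.50 | 1.38 |
| 4 | 0.535 | -0.233 | -2.293 | -0.50 | 2.29 |
| 5 | 1.604 | -0.699 | -2.293 | -1.50 | 3.82 |
| 6 | 2.673 | -1.399 | -1.911 | -2.74 | 9.17 |

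Systems 1 and 6 tie, although money per point is 100/15 = 6.7 against 600/3 = 200 thousand dollars. If lower is read as better, system 5 (second dearest, second least effective) outranks system 1. Using n instead of n - 1 in the SD leaves the ratios unchanged. Re-standardizing the combined cost only halves them, to -0.955 and -1.146.

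**Instability.** Hold c at -0.535. With o = 0.05 the ratio is -10.7; with o = -0.05 it is +10.7. A trivial shift in outcome across the mean moves the system from one extreme to the other.

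**Data without built-in symmetry.** In 20,000 random six-system sets at each of three cost-outcome correlations (normal draws, one cost score, lower ratio read as better):

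| Correlation | Sets where a dominated system scores better than one dominating it | Sets with both a cheap-effective and a dear-ineffective system |
|---|---|---|
| -0.5 | 99% | 96% |
| 0 | 95% | 82% |
| +0.5 | 86% | 55% |

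**Other scalings, same example.** Dividing by the SD or by the mean without centring keeps the order. Scores with mean 50 and SD 10 also keep it, but depend on an arbitrary origin. Min-max scaling gives the least effective system a zero denominator.

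**The case against.** The best reply is that the protocol never says z-scores. Dividing each variable by its SD or mean would also let dollars and hours be added, and it ranks the systems correctly as long as every outcome change is positive. That stands: a reader might infer that the ratio fails under any standardization, and the documents do not support this. They do not exclude the z-score reading either. It is the ordinary one, and the text claims comparability for standardized ratios without restriction. A statistical analysis plan could choose the scaling, but the ratio form and the comparability claim are already fixed here.

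A second reply is that the ratio is offered as something that can be done, not as a commitment, and stands beside a promised description of money and effort against change. That also stands. It would be wrong to infer that Objective 4 compares the systems through this ratio alone. It is, however, the only between-site index that the section names.

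Third, an exact tie needs matching magnitudes, and the example is symmetric by construction. This is true; the loss of sign information is general, and the simulated sets, which have no such symmetry, show how often it disturbs the order.

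A reader might also infer that adding money and hours counts paid staff time twice. The section lists the two separately and does not say that the financial figure includes wages, so this cannot be established. Equal weighting of the two is a judgement, not an error.

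**Conclusion.** The point holds in conditional form. If standardization means centring at zero across the six systems, the cost/outcome ratio cannot order them by the protocol's own criterion, and the statement "Because the ratios are standardized, one is able to compare the relative success of the six ENS" is wrong. The algebra is exact and needs no data. The size rests on assumptions: the tie at -1.91 comes from invented site values, and the 86% to 99% from normally distributed costs and outcomes with correlations between -0.5 and +0.5.

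This should be fixed, but it does not threaten the study. Objective 4 is descriptive, covers six systems and has no test attached. The defect does not touch data collection or Objectives 1 to 3, and it can be corrected at analysis.

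**What to change.** In Quantitative Objective 4, delete the ratio of centred scores and the sentence claiming that it makes the systems comparable. Replace them with:

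1. Money, personnel hours and outcome change for each of the six ENS in original units, with a plot of cost against outcome change.
2. Cost per unit of improvement, only for systems whose outcome change is positive.
3. If one unit-free index is wanted, standardized outcome minus standardized cost, with the outcome oriented so that higher is better and a statement that one SD of cost counts the same as one SD of outcome. In the example this gives 2.74, 1.50, 0.50, -0.50, -1.50, -2.74, the intended order.

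The cost is a few sentences. The difference index carries an arbitrary weighting, but a declared one. Money, hours and outcome changes are already inputs to the planned ratio, so no new data are needed.

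### If "standardize" means z-scores, Objective 4's cost/outcome ratio cannot rank the six ENS in line with the protocol's own definition of cost-effective

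*Protocol*

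**What the plan says.** Quantitative Objective 4 in the Protocol's Statistical Analysis section has three parts that matter here.

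- **Data and description.** Sites report "the total investment each site must make in its ENS, both in terms of financial commitments and in terms of personnel hours". The section commits to describing this spending against the changes seen in services, satisfaction and health outcomes.
- **Index.** For comparison across sites, "one can standardize and combine cost variables (money + effort"), and "then standardize outcome variables (e.g., health outcomes) and compute a ratio of <costs/outcome> for each of the six ENS". The justification follows at once: "Because the ratios are standardized, one is able to compare the relative success of the six ENS at promoting desired outcome changes at lower costs".
- **Criterion.** "Cost effective systems are those that achieve relatively greater (desired) changes for relatively less money or personnel hours expended".

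The section does not define the scaling. It gives no rule for a zero or negative denominator, and does not say how the sign of the ratio is to be read.

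**The concern.** A ratio of cost to effect ranks options only if the denominator is positive and both terms keep a true zero. Z-scoring across six ENS removes both properties. Each set of z-scores averages zero, so unless all values are equal, some costs and some outcome changes become negative. Division then merges opposite cases: low cost with high gain and high cost with low gain share one sign, while low cost with low gain and high cost with high gain share the other. An ENS near the six-site mean gain is divided by a number near zero.

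The stakes are practical. Evaluation question 3 in the Hypothesis section asks what goes with cost-effective improvement, and Aims 1 and 3 direct the findings at practice and policy. The index could present a system that costs more and achieves less than another as the most cost-effective of the six, and nothing in the number would reveal it.

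**Working it through.** The Protocol states no figure for Objective 4, so there is none to reproduce. It also gives no site costs or outcome changes, so **all site values below are assumed for illustration**. From the Protocol come the number of units (six ENS), the form of the index and the criterion. The Protocol does not say which end of the ratio is best. I take the lowest as best, as a cost-over-outcome ratio implies.

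**Formulas.** z = (x - mean)/SD across the six ENS, with the n-1 SD; ratio = z(cost)/z(gain). Building cost as z(money) + z(hours) changes nothing essential, because that sum also averages zero.

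**Example 1: sign cancellation.** Mean cost is 500, SD = √(105,000/5) = 144.9. Mean gain is 10, SD = √(82/5) = 4.05.

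| Cost | Gain | z(cost) | z(gain) | Ratio | Cost per point | z(gain) - z(cost) |
|---|---|---|---|---|---|---|
| 300 | 16 | -1.38 | 1.48 | -0.93 | 18.75 | 2.86 |
| 400 | 11 | -0.69 | 0.25 | -2.79 | 36.36 | 0.94 |
| 450 | 8 | -0.35 | -0.49 | 0.70 | 56.25 | -0.15 |
| 550 | 12 | 0.35 | 0.49 | 0.70 | 45.83 | 0.15 |
| 600 | 9 | 0.69 | -0.25 | -2.79 | 66.67 | -0.94 |
| 700 | 4 | 1.38 | -1.48 | -0.93 | 175.00 | -2.86 |

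The cheapest ENS with the largest gain ties with the dearest ENS with the smallest gain, although their costs per point are 18.75 and 175. The lowest ratio is shared by 400/11 and 600/9. Both are dominated by 300/16, which is cheaper and better. Taking the highest ratio as best does not help: the two ENS at 0.70 would lead, and 300/16 would still tie with 700/4.

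**Example 2: near-average gain.** Costs 200, 300, 400, 500, 600, 700; gains 20, 6, 10.1, 14, 9.9, 0 (mean 10). The ENS with gains 10.1 and 9.9 have z(gain) of +0.015 and -0.015 and get ratios of -18.2 and -54.6. The best ENS (200 for 20) and the worst (700 for 0) both get -0.91. The lowest ratio goes to the ENS that pays 600 for 9.9, which is dominated by the one that pays 200 for 20.

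**Simulation.** 200,000 sets of six ENS, normal cost and gain, z-scored within each set, lowest ratio taken as best:

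| Correlation of cost and gain | Lowest-ratio ENS dominated by another |
|---|---|
| -0.5 | about 65% |
| 0 | 58% |
| 0.5 | about 50% |
| 0.8 | about 41% |

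With independence, the lowest-ratio ENS is above average in cost and below average in gain in 49% of sets, and at least one ratio exceeds 10 in absolute value in 30%.

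**Scaling without centring.** With costs 200 to 700 in steps of 100 and gains 20, 16, 12, 8, 4, 1, dividing each variable by its mean gives 0.23, 0.42, 0.75, 1.41, 3.39, 15.81, which is the right order. Dividing by the SD also orders them correctly (0.39 to 27.02). Now change the last gain from 1 to -1, so that the mean gain becomes 59/6 = 9.83. The dearest ENS, the only one that worsened, scores (700/450)/(-1/9.83) = -15.3. That is the lowest ratio, and so nominally the best.

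**Mixed case.** If cost is left positive and only the outcome is centred, every ENS below the mean gain gets a negative ratio and sorts ahead of all those above it.

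**The case against.** The strongest reply is that the Protocol never says z-score, centring or SD. Dollars and hours can also be made additive by dividing each by its mean or SD, and a change divided by its SD is a plausible reading of a standardized outcome. On that reading, with all changes positive, the ratio ranks the ENS correctly. This stands, and it makes the finding conditional. A reader might infer that the ratio fails under any scaling; the text does not support that. But z-scoring is the ordinary meaning of standardizing a variable, and the section does not exclude it. The uncentred alternative needs every change to be positive, which nothing in the section ensures.

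Second, the index is offered in permissive wording, whereas the committed analyses under Objective 1 are stated as what will be done. A reader might also infer that this ratio is the only cost-effectiveness analysis planned. It is not: the section first commits to describing spending against change, and that description is untouched and could expose a dominated ENS. Still, the ratio is the only cross-site calculation given, and the claim that it permits comparison carries no condition.

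Third, a statistical analysis plan, not available here, could define the scaling. That would be an answer to missing detail. The point here is a stated index paired with a stated justification that fails under the index's usual meaning.

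Fourth, the figures are illustrative: Example 1 was chosen to give exact ties, and independence of cost and gain is an assumption. The percentages depend on the correlation, hence the range. The sign cancellation and the division near zero do not.

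**Conclusion.** The point holds conditionally. If "one can standardize and combine cost variables (money + effort") and the matching step for outcomes mean z-scores across the six ENS, the ratio cannot order the ENS by the section's own criterion, and the assertion "Because the ratios are standardized, one is able to compare the relative success of the six ENS" does not follow. The lowest-ratio ENS is then dominated by another in 58% of simulated sets under independence, and in about 41% to 65% for cost-gain correlations from 0.8 to -0.5. These shares rest on assumed normal site values, not on trial data. If the scaling is uncentred, the index works only when every change is positive.

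Severity is moderate. Objective 4 is a descriptive comparison of six units, with no test or sample size attached, in an evaluation that the Hypothesis section frames by questions instead of scientific hypotheses. A reader might infer that the flaw undermines the evaluation as a whole. It does not: it affects one suggested index.

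**What to change.** Reword one paragraph of Quantitative Objective 4; no new data are needed.

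- Delete the ratio of standardized values and the sentence saying that it permits comparison.
- Build on the description of spending against change that the section already promises: plot each ENS's cost and outcome change in natural units, showing money and personnel hours separately or combined on a stated basis.
- Flag any ENS that another ENS beats on both cost and change.
- Report cost per unit of improvement only for an ENS whose change is in the desired direction.
- If a single index is wanted, use z(change) minus z(cost), with every outcome signed so that higher is better. It never divides by a value near zero, and in Example 1 it runs from 2.86 for the best ENS to -2.86 for the worst. State openly that it gives one SD of cost the same weight as one SD of benefit, which is a choice and not a finding.

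### Objective 4 compares the six ENS on one point value each, but a single site's 100 patients per wave leave a chance spread in outcome change about as large as the 10-point planning effect, or larger

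*Protocol*

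**What the plan says.** The Objective 4 paragraph under Statistical Analysis records "the total investment each site must make in its ENS", in money and personnel hours, and relates it to how far services, satisfaction and health outcomes change. It proposes to standardize costs and outcomes and "compute a ratio of <costs/outcome> for each of the six ENS". It then infers from the standardized scale that "one is able to compare the relative success of the six ENS at promoting desired outcome changes at lower costs". Its last sentence labels as cost effective those systems with comparatively larger desired change for comparatively less outlay.

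The Sample Size section gives the only statement of precision, in the same terms for the patient survey and the data extraction: "A sample of 100 per site (N=600 per observation period) will give us 80% power to detect 10% change in proportional outcomes", with 50% to 60% as the example, "using a two-sided test with 0.05 alpha". It adds: "This estimate assumes an intra-class correlation (ICC) of 0.005". The patient count is built as "100 people per site per wave; 6 sites; 5 waves". That is a maximum, reached if no patient recurs, so overlap between waves is left open.

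Mixed models that adjust for baseline differences across the six ENS are planned under Objective 1. Objective 4 does not refer to them.

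**The concern.** Each site has its own ENS, so the outcome side of each ratio comes from that site's patients alone. The rule in Objective 4 uses one point value per system and grades systems relative to each other. Six systems with identical effects would still yield six different values, and the rule would label some of them more cost effective than others. The reason the protocol gives for comparability, that the ratios are standardized, does not address this: identical systems and truly different ones look alike once both are put on a common unit of spread.

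Aims 1 and 3 direct the findings at practice and policy. A statement that one named system is more cost-effective than another could therefore be acted on when the difference in outcome change is within sampling error.

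**Working it through.** **Inputs from the protocol.** 100 patients per site per wave; six sites, one ENS each; 600 per wave in total; example 50% to 60%; two-sided alpha 0.05; ICC 0.005; one wave before rollout and four after.

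**1. The protocol's own figure.**
- Design effect: 1 + (100 − 1) × 0.005 = 1.495.
- Effective n per wave: 600 / 1.495 = 401.
- Power for 50% against 60%, two-sided 0.05: 81.4%.

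The stated 80% is confirmed for the pooled change.

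**2. One site, one wave before and one after, different patients.**
- SE of the change: √(0.5 × 0.5/100 + 0.6 × 0.4/100) = √0.0049 = 7.0 points.
- 95% half-width: 1.96 × 7.0 = 13.7 points.
- Power for the same 10-point change at one site: 29%.
- SE of the difference between two sites' changes: √(2 × 0.0049) = 9.9 points. Power when the true changes differ by 10 points: 17%.

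**3. Six systems, all truly gaining 10 points.** The mean range of six standard normal values is 2.534, so the expected best-to-worst gap is 2.534 × 7.0 = 17.7 points. Binomial simulation (400,000 runs) agrees:
- mean gap 17.7 points, central 95% of gaps 7 to 30;
- gap of 10 points or more in 93% of runs;
- at least one system with zero or negative change in 42%.

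**4. One system truly 5 points better than the other five.** It shows the largest change in about 36% of runs with one post-rollout wave and about 42% with four pooled. Picking at random would give 1/6 = 17%.

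**5. Other assumptions the protocol leaves open.** For the same patients followed at correlation r, SE² = 0.0025 + 0.0024 − 2r√(0.25 × 0.24)/100. For four pooled post-rollout waves, SE = √(0.25/100 + 0.24/400) = 5.6 points.

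| Setting | 95% half-width (points) | Expected chance gap (points) |
|---|---|---|
| One wave before, one after, different patients | 13.7 | 17.7 |
| Four post-rollout waves pooled | 10.9 | 14.1 |
| Linear trend over five waves | 12.3 | 15.9 |
| Same patients, r = 0.3 | 11.5 | 14.8 |
| Same patients, r = 0.5 | 9.7 | 12.5 |
| Same patients, r = 0.7 | 7.5 | 9.7 |
| Rates near 80% | 11.1 | 14.3 |
| Rates near 90% | 8.3 | 10.7 |
| Stated ICC added as site-by-wave variation | 16.8 | 21.7 |

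**6. The ratio itself.** If standardizing means z-scores across the six sites (the protocol does not define it), a system one SD cheaper and one SD better scores −1/1 = −1. A system one SD dearer and one SD worse scores 1/(−1) = −1, the same value. The denominator can also fall near zero, so an interval placed on this ratio would be unstable.

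**The case against.** The strongest reply is that Objective 4 is descriptive and permissive: it says what one can compute, names no test and no formal ranking, and leaves intervals to an analysis plan that is not at hand. Part of this stands. The absence of an interval method would not be a finding by itself. What remains is the protocol's own inference that standardizing makes the six systems comparable, and a closing sentence that labels systems by relative change. Neither is conditional.

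Four stronger readings are tempting, and the document does not support them:

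- A reader might infer that Objective 4 uses raw before-after changes. The protocol does not say how change is estimated. The Objective 1 models are neither required nor excluded.
- A reader might infer that the cost-effectiveness comparison would be mostly chance. That is not shown. Cost is recorded per site, not sampled from patients, and every figure above concerns outcome change alone. The combined measure has not been computed.
- A reader might infer that standardizing makes the noise worse. Z-scoring is linear. It hides absolute size, but changes neither the ordering of outcomes nor the ratio of signal to noise.
- A reader might infer that the power statement is wrong. It is correct for the pooled change and claims nothing about single sites.

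It is also fair to say that the 17.7-point figure comes from a rather unfavourable case: rates near 50%, one post-rollout wave and no patient overlap. More favourable settings narrow it, though in most of them the gap still exceeds 10 points.

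**Conclusion.** The point holds in limited form and should be acted on. The stated reason for comparing the six ENS does not support the comparison, because sampling error at a single site survives standardizing and the rule has only a point value per system. Among the settings tabulated, the chance gap in the outcome component runs from about 10 to about 22 points, against a planning effect of 10. The low end needs the same patients followed at correlation 0.7; the high end adds the stated ICC as site-by-wave variation. All figures assume a binary outcome and equal true effects across the six sites, except the scenario with one system 5 points better. They say nothing about the cost side.

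**What to change.** Amend Objective 4 as follows:

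1. Take each ENS's outcome change from the Objective 1 mixed model, using all post-rollout waves.
2. Report 95% intervals for each site's change and for differences between ENS. Use model-based intervals, or resample whole patients within site so that repeat measurements on a patient stay together. Resampling each wave separately would break that pairing where patients overlap.
3. Show change, with its interval, against cost in natural units, for example as a cost-versus-change plot, in place of reliance on a ratio of z-scores.
4. Replace the closing rule: describe one ENS as more cost-effective than another only where the interval for the difference supports it, and otherwise present the comparison as descriptive.
5. State in Sample Size that the 80% power applies to the pooled change only.

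This needs no new data. It costs some rewording and a little more analysis work. With only six sites, any between-site variance in the model will be poorly estimated, and this should be acknowledged. The main downside is fewer definite comparisons between systems.
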